## LIST OF ABBREVIATIONS

**CE: Ethics Committee**

**CI: Informed Consent**

**CRF: Case Report Form (Data Collection Form)**

**GCP: Good Clinical Practice**

**AIHA: Autoimmune Hemolytic Anemia**

**ITP: Immune Thrombocytopenia (formerly Idiopathic Thrombocytopenic Purpura)**

**CIN: Chronic Idiopathic Neutropenia**

### 1. **INTRODUCTION**

|            |                   |            |                  |
|------------|-------------------|------------|------------------|
| 1.1 | Background | and | Rationale |
|------------|-------------------|------------|------------------|

Autoimmune cytopenias, including autoimmune hemolytic anemia (AIHA), immune thrombocytopenia (ITP), and chronic idiopathic neutropenia (CIN), are rare and benign hematological conditions characterized by the production of autoantibodies or the development of autoreactive T lymphocyte clones capable of attacking circulating blood cells (red blood cells, platelets, and neutrophils) or inducing premature death of precursors in the bone marrow (ineffective erythropoiesis). Autoimmune cytopenias represent a spectrum of disease ranging from mild, often asymptomatic forms diagnosed incidentally, to severe and potentially fatal forms. The latter typically manifest acutely with symptoms of severe anemia (fatigue, shortness of breath, anginal pain, etc.), thrombocytopenia (mucosal or cutaneous bleeding of varying severity), or neutropenia (acute, chronic, or recurrent infections). In addition to the direct consequences of immune cytopenias, associated complications related to the disease or therapies may occur, including thrombosis, infections, and acute or chronic renal failure. Moreover, the three cytopenias may be variably associated, forming Evans syndrome.

Currently, the main predictor of severity, relapse, and onset of complications used by clinicians is the severity of cytopenia at onset: for example, patients with severe anemia (Hb <6 g/dL) have approximately double the risk of relapse compared to those with moderate or mild anemia. Another known risk factor for relapse is the presence of Evans syndrome. Infectious complications and acute renal failure correlate with mortality, which for autoimmune hemolytic anemia is estimated to be around 10%.

Despite this limited evidence, the rarity of these diseases and the lack of adequate prospective studies make prognostic assessment and management—especially during the two most critical phases, onset (especially if acute) and severe relapses requiring multiple therapy lines and hospitalization—difficult. During these phases, it may be necessary to tailor the aggressiveness of therapy and potential transfusional support based on numerous clinical and laboratory data that are not yet standardized. For example, it is currently unknown which patients should receive anticoagulant prophylaxis, except

[figure not shown][figure not shown]

Dipartimento di Medicina Interna  
UOC EMATOLOGIA  
Pad. Marcora / Granelli  
Direzione [contact]  
Amb: [name] - DH: [name]  
Reparti: CTMO [name] - AOE [name]  
Mail: [contact]

- Direttore: [name]

for those with known additional risk factors (diabetes, obesity, factor V Leiden or prothrombin mutation, etc.).

On the other hand, the availability of new drugs for autoimmune cytopenias (rituximab, thrombopoietin receptor agonists, complement inhibitors, fostamatinib, neonatal Fc receptor inhibitors, and tyrosine kinase inhibitors) makes it even more necessary to identify ideal candidates for treatment and predictive factors for relapse, non-response, and complications, particularly infections. This would improve therapeutic choices and monitoring of complications.

Finally, some patients with isolated cytopenia show bone marrow features such as dysmyelopoiesis and clonal cell populations (myeloid or lymphoid), potentially evolving into overt hematologic malignancies. Currently, there are no tools to predict this evolution risk, and studying somatic DNA mutations via targeted sequencing could provide insights.

From a diagnostic standpoint, the list of tests to use in each autoimmune cytopenia is not standardized, requiring continuous exchange of information between the clinician in charge (e.g., internal medicine specialist) and the hematologist. A critical evaluation of the tests used, their sensitivity and specificity, and the discharge diagnoses of hospitalized cytopenic patients could provide important information for diagnostic pathway rationalization.

Based on these considerations, AIHA, ITP, and CIN require more standardized approaches, both in routine tests (CBC, hemolysis indices, autoimmunity markers, electrophoresis, etc.) and experimental markers such as somatic DNA mutations, levels of specific immunomodulatory cytokines, lymphocyte subpopulations, and the microbiota. The microbiota, which comprises the microbial flora colonizing specific body districts (e.g., respiratory and intestinal tracts), is increasingly recognized as an active player in autoimmune disease pathogenesis and complications. Studying its complexity at diagnosis and various time points during treatment could provide crucial information on relapse risk and especially infection risk in these often heavily immunosuppressed patients.

The aim of this project is to critically evaluate the diagnostic and therapeutic pathway of patients with autoimmune cytopenia, particularly those hospitalized at this hospital, to create a list of diagnostic tests appropriate for different clinical levels and identify prognostic and predictive markers for relapse, therapeutic response, and complications including death. Secondly, it will evaluate whether the study of somatic DNA mutations, cytokine profiles, lymphocyte subpopulations, and respiratory and intestinal microbiota can serve as valid and accurate tools to provide information on disease severity, relapse tendency, and infection risk. If this working hypothesis proves valid, it could justify exploring these parameters at diagnosis and during treatment, potentially developing dynamic biomarkers anticipating relapse or severe infections.

---

## 2. STUDY OBJECTIVES

### 2.1 Primary Objective

- Characterize the diagnostic pathway of newly diagnosed autoimmune cytopenia patients hospitalized or attending the Hematology outpatient clinics of this hospital.

[figure not shown][figure not shown]

Dipartimento di Medicina Interna  
UOC EMATOLOGIA  
Pad. Marcora / Granelli  
Direzione [contact]  
Amb: [name] - DH: [name]  
Reparti: CTMO [name] - AOE [name]  
Mail: [contact]

- Direttore: [name]

- Determine sensitivity and specificity of the tests used and prepare a list of recommended diagnostic tests for autoimmune cytopenia at various clinical levels.

## 2.2 Secondary Objectives

- Evaluate clinical and laboratory markers predictive of therapeutic response and complications, particularly infections, through longitudinal collection of clinical data, serum/plasma/bone marrow samples, nasopharyngeal swabs, and fecal samples during the observational study period.
- Preliminary correlation analysis between identified somatic DNA mutations, cytokine patterns, microbiota complexity at diagnosis and during disease course with therapeutic response, relapses, and complications (especially infections).
- Evaluate red blood cell metabolism in a subgroup of patients with cytopenias and bone marrow dysplasia and measure in vitro activity of glycolysis-activating drugs (specific substudy objective).

---

## 3. STUDY DESIGN

### 3.1 Design

The study will enroll patients with anemia ( $Hb < 12 \text{ g/dL}$ ), thrombocytopenia (platelets  $< 100,000/\text{mm}^3$ ), and neutropenia (neutrophils  $< 1000/\text{mm}^3$ ) without prior hematologic diagnosis, hospitalized or attending Hematology outpatient clinics. Diagnosis of autoimmune cytopenia will follow current accepted criteria for AIHA (evidence of hemolysis and positive/negative direct Coombs test after exclusion of other hemolysis causes), ITP (exclusion of other thrombocytopenia causes, with or without anti-platelet antibodies), and CIN (exclusion of other neutropenia causes, with or without anti-neutrophil antibodies).

To ensure informative clinical follow-up on test sensitivity and specificity and to establish a control group, all newly diagnosed cytopenia patients without known primary cause will be enrolled. Patients will be classified by severity and, for AIHA, by antibody characteristics:

- Moderate ITP: platelets  $> 30,000/\text{mm}^3$
- Severe ITP: platelets  $< 30,000/\text{mm}^3$
- Mild neutropenia: neutrophils  $> 1000/\text{mm}^3$
- Moderate neutropenia: neutrophils  $500\text{--}1000/\text{mm}^3$
- Severe neutropenia: neutrophils  $< 500/\text{mm}^3$
- Warm AIHA: monospecific direct Coombs positive for IgG or IgG+C low titer, no autoagglutination at  $20^\circ\text{C}$
- Cold AIHA: monospecific direct Coombs positive for C3d fraction and/or cold agglutinins with or without autoagglutination at  $20^\circ\text{C}$

[figure not shown][figure not shown]

Dipartimento di Medicina Interna  
UOC EMATOLOGIA  
Pad. Marcora / Granelli  
Direzione [contact]  
Amb: [name] - DH: [name]  
Reparti: CTMO [name] - AOE [name]  
Mail: [contact]

- Direttore: [name]

- Mixed AIHA: monospecific direct Coombs positive for high-titer IgG+C and autoagglutination at 20°C and/or dual specificity for anti-Rh and anti-I/i/IH
- Atypical AIHA: monospecific direct Coombs positive for IgA, for warm IgM, or direct Coombs negative after exclusion of other hemolysis causes.

Availability of clinical information at diagnosis and follow-up updates for at least 3 years are key inclusion criteria.

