### 3.2 Inclusion Criteria

Patients fulfilling all the following:

- New diagnosis of cytopenia without known secondary cause
- Male or female  $\geq 18$  years old
- Able to provide informed consent
- Willing to undergo regular clinical follow-up for 3 years after enrollment

For substudy participation, additional criteria:

- Bone marrow evaluation.

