## 6. STUDY DURATION/TIMELINE

Enrollment is expected to be completed within 2 years.

All patients included in the study will have a minimum follow-up of 3 years.

At the end of the enrollment phase, it will be evaluated whether the sample size is consistent with the preliminary enrollment estimates. Otherwise, enrollment will be extended by an additional 12 months.

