## 7. EXPERIMENTAL DESIGN

### 7.1 Sample size

On average, our Center annually evaluates 40 new patients with autoimmune hemolytic anemia (AIHA), 40 with immune thrombocytopenia (ITP), and 20 with cytopenia of undetermined significance (CIN). Therefore, enrollment of at least 200 patients is expected. Considering that the relapse risk is approximately 30% in AIHA and ITP and most relapses occur within the first 24 months from onset, it is reasonable to estimate that about 40-50 patients will experience relapse during the three-year follow-up.

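### Section 3.1 makes 3 years of available follow-up an entry condition, which cannot be judged at enrolment, conflicts with Section 3.2 and, if applied literally, removes early deaths and losses

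*Protocol*

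**What the plan says.** Three places in the protocol deal with follow-up as a condition of membership.

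- Section 3.1 (Design) closes with: "Availability of clinical information at diagnosis and follow-up updates for at least 3 years are key inclusion criteria".
- Section 6 (Study duration/timeline) says: "All patients included in the study will have a minimum follow-up of 3 years". Neither sentence makes an exception for death, withdrawal or loss.
- Section 3.2 (Inclusion Criteria), the formal list, requires only that the patient be "Willing to undergo regular clinical follow-up for 3 years after enrollment".

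Section 3.1 also says, before the sentence above, that every patient with a newly found cytopenia of no known primary cause will be taken in, partly to provide a control group.

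The aim at the end of Section 1 includes finding markers for relapse, response and complications, and counts death among the complications. The background in the same section says: "Infectious complications and acute renal failure correlate with mortality, which for autoimmune hemolytic anemia is estimated to be around 10"%. The Statistical analysis section relates markers to response, relapse-free survival (RFS) and three complications (thrombosis, acute renal failure, infections). RFS is to be analysed by Kaplan-Meier with a log-rank test or Cox model.

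**The concern.** Willingness to be followed can be established at the enrolment visit. Availability of 3 years of updates cannot, because patients join at new diagnosis and the data lie in the future. An investigator who takes the 3.1 sentence as an inclusion criterion can apply it only in retrospect, by removing patients whose follow-up stopped early.

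The analysed cohort would then consist of people who survived and stayed in contact for 3 years. Observed 3-year mortality would be zero by construction, although the aim names death. Infections and acute renal failure are among the complications to be related to markers, and the protocol says they correlate with mortality, so patients with those events would probably be over-represented among those removed. Complication rates, relapse and RFS results, and marker associations could all shift toward milder disease.

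The primary endpoint, the count of laboratory tests needed for diagnosis, is settled at diagnosis. It would change only if the removed patients needed a different number of tests from the rest.

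**Working it through.** **Inputs from the protocol**

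- Annual intake (Section 7.1): "our Center annually evaluates 40 new patients with autoimmune hemolytic anemia (AIHA), 40 with immune thrombocytopenia (ITP), and 20 with" CIN.
- Enrolment period (Section 6): "Enrollment is expected to be completed within 2 years".
- Cohort size (Section 7.1): "enrollment of at least 200 patients is expected".
- Relapse (Section 7.1): "the relapse risk is approximately 30% in AIHA and ITP and most relapses occur within the first 24 months from onset".
- AIHA mortality (Section 1): around 10%, no time horizon.

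**The plan's own figures**

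- Cohort: (40 + 40 + 20) × 2 = 200, as stated.
- Relapses: 0.30 × (80 AIHA + 80 ITP) = 48, within the stated 40–50.

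Both figures use the full intake, with no deduction for deaths or losses.

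**Effect of the literal 3.1 condition: deaths**

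Assume that the 10% AIHA mortality falls entirely within 3 years.

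- AIHA patients removed: 0.10 × 80 = 8.
- Share of the expected cohort: 8 / 200 = 4%, leaving 192.

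This is the only part of the size that rests on a protocol figure. It is an upper figure for AIHA deaths at that mortality, since any death after 3 years would not count.

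**What losses and other deaths could add (assumed rates only)**

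The protocol gives no ITP or CIN mortality and no rate of loss. With m the assumed mortality in the 120 ITP and CIN patients, and l the assumed loss among those who do not die:

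removed = (8 + 120m) + l × (200 − 8 − 120m)

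| m | l | Deaths | Lost | Removed | % of 200 |
|---|---|---|---|---|---|
| 0 | 0 | 8 | 0 | 8 | 4.0 |
| 0 | 5% | 8 | 9.6 | 17.6 | 8.8 |
| 0 | 20% | 8 | 38.4 | 46.4 | 23.2 |
| 10% | 20% | 20 | 36 | 56 | 28.0 |

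Everything below the first row depends on rates that I assumed.

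**Possible shift in the AIHA relapse rate**

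If 30% of AIHA patients relapse overall, 10% die, and a fraction r of those who die had relapsed, the rate among the retained is (0.30 − 0.10r) / 0.90.

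- r = 0.30: 0.27 / 0.90 = 30.0%, or 21.6 relapses among 72 retained.
- r = 1.00: 0.20 / 0.90 = 22.2%, or 16 among 72.

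The full AIHA intake gives 0.30 × 80 = 24. The rate is therefore unbiased if relapse is unrelated to death and falls by up to about 8 percentage points at the extreme. The protocol gives no value for r.

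**If Section 3.2 governs**

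All 200 patients and about 48 relapses stay in, and the bias does not arise.

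**The case against.** The strongest reply is that Section 3.2 is the operative list and is sound. The 3.1 sentence closes a descriptive section and may be a loose paraphrase of the 3.2 item. Section 6 can be read as timeline wording: the study stays open until the last patient reaches 3 years.

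Other text supports that reading. Section 3.1 intends to enrol all new patients, Section 7.1 counts the full intake, Section 10.2.3 lets patients withdraw at any time, and Kaplan-Meier and Cox methods accommodate censoring. Section 3.1 also links follow-up to informative estimates of sensitivity and specificity, so there is a reason for wanting 3 years.

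Much of this stands, and it rules out several stronger readings that a reader might infer:

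- *That the plan will drop enrolled patients.* No section says so; it is only what the literal 3.1 rule would require.
- *That fatal cases are the ones with infection or renal failure.* Section 1 claims only a correlation with mortality.
- *That loss to follow-up is itself an outcome to be predicted.* It is not named as one anywhere. It matters only as possibly informative selection.
- *That death is a formal endpoint.* It appears in the aim, but not in the objectives, the endpoints or the complications listed for analysis.
- *That the primary result is invalidated.* It is fixed at diagnosis, in a study described as purely descriptive.
- *That RFS loses every early death.* RFS starts at response, so patients who die before responding never enter it under either reading.

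What does not stand is treating the conflict as harmless. Section 3.1 labels its condition a key inclusion criterion, and no text says that 3.2 takes precedence. Wanting long follow-up to confirm diagnoses does not require excluding patients whose diagnosis was already settled when follow-up ended. Eligibility is fixed in the protocol, so this is not detail that can be left to a statistical analysis plan.

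**Conclusion.** The entry rule is wrong as written. Section 3.1, reinforced by Section 6, states a condition that cannot be assessed at entry and that contradicts both Section 3.2 and the commitment in 3.1 to enrol all new patients. If applied, it would bias the secondary prognostic analyses (complications, relapse and RFS, and death as named in the aim) toward milder disease. The primary endpoint would be affected only through cohort selection.

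The size supported by the protocol's figures is modest: about 8 of 80 AIHA patients, 4% of 200, provided that the 10% mortality falls within 3 years. Losses to follow-up would enlarge it by an amount the protocol does not allow one to state. If Section 3.2 is what the investigators will follow, there is no bias and the remaining task is to make the text agree.

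**What to change.** Three changes in one amendment:

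1. In Section 3.1, delete the condition on availability of 3 years of follow-up, so that the willingness criterion in Section 3.2 governs.
2. In Section 6, replace the minimum with *planned follow-up of 3 years, or until death or withdrawal*.
3. State that all enrolled patients stay in the analysis, and that those who die or are lost contribute data up to that point. Deaths are reported as an outcome or a competing event, and losses are censored at last contact. The stated RFS definition (from response to relapse) stays unchanged.

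The cost is a few sentences, with no new procedures, data or enrolment. The downside is that some patients will have incomplete follow-up, which the planned Kaplan-Meier and Cox methods handle, subject to the usual assumption that censoring is not informative.

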### 3.2 Inclusion Criteria

Patients fulfilling all the following:

- New diagnosis of cytopenia without known secondary cause
- Male or female  $\geq 18$  years old
- Able to provide informed consent
- Willing to undergo regular clinical follow-up for 3 years after enrollment

For substudy participation, additional criteria:

- Bone marrow evaluation.

### 3.3 Exclusion Criteria

Patients with any condition potentially interfering with protocol adherence or informed consent.

---

## 4. STUDY PROCEDURES

### 4.1 Intervention

Enrollment:

- Venous blood draw for somatic DNA mutation and cytokine profile studies
- Nasopharyngeal swab and fecal sample for microbiota analysis
- Medical history, physical exam, anthropometrics
- Blood, urine, and instrumental tests as clinically indicated to assess hematologic disease status
- For the marrow substudy, samples will be used to study immunological microenvironment, cytokine patterns, and RBC metabolism.

Follow-up (every 1–3 months for AIHA and ITP, every 6–12 months for CIN, according to clinical need):

- Blood for cytokine profiling
- Nasopharyngeal swab and fecal sample for microbiota analysis

[figure not shown][figure not shown]

Dipartimento di Medicina Interna  
UOC EMATOLOGIA  
Pad. Marcora / Granelli  
Direzione [contact]  
Amb: [name] - DH: [name]  
Reparti: CTMO [name] - AOE [name]  
Mail: [contact]

- Direttore: [name]

- Medical history, physical exam, anthropometrics
- Blood, urine, instrumental tests as indicated

At relapse:

- Blood/marrow, nasopharyngeal swab, fecal sample, clinical evaluation, and lab tests as above. Samples stored at the Hematology and Transfusion Medicine Laboratory biobank.

## 5. ENDPOINT

### 5.1 Primary endpoint

Number of laboratory tests required to reach the diagnosis of autoimmune cytopenia for each patient.

### 5.2 Secondary endpoints

Type of laboratory tests required to reach the diagnosis of autoimmune cytopenia and to investigate physiopathology of the disease.

Number and type of imaging tests required to reach the diagnosis of autoimmune cytopenia.

## 6. STUDY DURATION/TIMELINE

Enrollment is expected to be completed within 2 years.

All patients included in the study will have a minimum follow-up of 3 years.

At the end of the enrollment phase, it will be evaluated whether the sample size is consistent with the preliminary enrollment estimates. Otherwise, enrollment will be extended by an additional 12 months.

## 7. EXPERIMENTAL DESIGN

### 7.1 Sample size

On average, our Center annually evaluates 40 new patients with autoimmune hemolytic anemia (AIHA), 40 with immune thrombocytopenia (ITP), and 20 with cytopenia of undetermined significance (CIN). Therefore, enrollment of at least 200 patients is expected. Considering that the relapse risk is approximately 30% in AIHA and ITP and most relapses occur within the first 24 months from onset, it is reasonable to estimate that about 40-50 patients will experience relapse during the three-year follow-up.

### 7.2 Procedures

All procedures will be conducted at the laboratory of the UOS Anemia Pathophysiology, Mangiagalli Pavilion ground floor, part of the UOC Hematology.

### Molecular profiling analysis

Somatic mutations in genes reported to be associated with myeloid pathology potentially linked to the pathogenesis or clinical behavior of autoimmune cytopenias will be analyzed. Whole exome sequencing (WES) will be performed, focusing first on genes involved in proliferation/apoptosis pathways (RAS, TP53), DNA methylation (IDH1/IDH2, DNMT3A, TET2, ASXL1), and RNA splicing (SF3B1, NOTCH), and then extended to possible pathogenic variants. WES analysis will be based on a target enrichment system for next generation sequencing (NGS), allowing efficient, simple, and rapid analysis of genomic regions of interest in a large number of samples. For NGS, 50 ng of non-amplified genomic DNA from peripheral blood mononuclear cells will be enriched for target exons by liquid-

[figure not shown][figure not shown]

Dipartimento di Medicina Interna  
UOC EMATOLOGIA  
Pad. Marcora / Granelli  
Direzione [contact]  
Amb: [name] - DH: [name]  
Reparti: CTMO [name] - AOE [name]  
Mail: [contact]

- Direttore: [name]

phase hybridization using a SureSelect custom kit designed to capture all coding exons ( $n = 2,045$ ) of 104 target genes (Agilent Technologies), according to an optimized automated processing protocol. After attaching index sequences to discriminate respective samples, the enriched target DNA will undergo massive parallel sequencing using a NextSeq 550 sequencer (Illumina) with a default protocol of 150 bp paired-end reads. Sequencing results will be analyzed through our pipeline to identify somatic mutations. All sequencing reads will be aligned to the human reference genome (hg19) using BWA version 0.5.8 with standard parameters. After removing duplicate or low-quality reads, allele frequencies of single nucleotide variants (SNVs) and indels at each genomic position will be calculated by enumerating relevant reads using samtools. Variants with allele frequency  $>2\%$  and supported by  $>5$  reads will be extracted and annotated using ANNOVAR28. Synonymous and ambiguous variants will be discarded.

Missense SNVs already present in public and private single nucleotide polymorphism (SNP) databases and missense SNVs with allele frequency between 0.45 and 0.55 will be filtered as polymorphisms. Among missense SNVs with allele frequency 0.45–0.55, known hotspot mutations will be considered somatic mutations. The significance of observed mutations in each gene will be assessed by calculating the type I error under the null hypothesis that all observed non-silent mutations are "passenger changes," assuming a Poisson distribution with a uniform background mutation rate ( $\lambda$ ).

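### Both germline filter rules apply only to missense SNVs, so inherited indels and nonsense variants, and some uncatalogued missense SNVs, are retained as somatic

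*Protocol*

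**What the plan says.** All of this is in the protocol, section 7.2, under Molecular profiling analysis.

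- **Source DNA:** "50 ng of non-amplified genomic DNA from peripheral blood mononuclear cells". No matched germline sample is named. The matched control donors in the cytokine section serve the cytokine measurements.
- **Variant classes:** "allele frequencies of single nucleotide variants (SNVs) and indels at each genomic position will be calculated by enumerating relevant reads using samtools". Variants above 2% allele frequency with more than 5 supporting reads "will be extracted and annotated using ANNOVAR28". There is no upper limit on allele frequency.
- **General discard:** "Synonymous and ambiguous variants will be discarded". The second of these two terms is not defined.
- **Polymorphism filter:** "Missense SNVs already present in public and private single nucleotide polymorphism (SNP) databases and missense SNVs with allele frequency between 0.45 and 0.55" are filtered out.
- **Exception:** "Among missense SNVs with allele frequency 0.45–0.55, known hotspot mutations will be considered somatic mutations".
- **Use of the remaining calls:** "The significance of observed mutations in each gene will be assessed by calculating the type I error", counting non-silent mutations against a uniform Poisson background rate. Section 2.2 adds a preliminary correlation of the somatic mutations with response, relapse and complications.

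**The concern.** The pipeline is meant to find somatic mutations without a germline comparator, so everything depends on the filter. Both filter rules name one variant class, missense SNVs, while the calling step takes in more. An inherited frameshift or nonsense variant therefore meets no germline rule. The window is also fixed, although the scatter of an observed allele frequency around 0.5 depends on read depth.

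If inherited variants stay in the somatic set, patients without a clone are counted as mutated. Mutation frequencies are inflated, a gene can show an excess in the Poisson test for reasons unrelated to somatic selection, and any real association with clinical course is diluted. Section 7.1 expects only about 40-50 relapses, which leaves little room for such misclassification.

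**Working it through.** The protocol gives no sequencing depth, variant count or false-call rate, so there is no figure of its own to reproduce.

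**Step 1. Trace each kind of inherited variant through the two rules as written.**

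| Inherited variant | Database rule | 0.45-0.55 window | Result |
|---|---|---|---|
| Missense SNV, catalogued, any zygosity | removes it | not needed | removed |
| Missense SNV, uncatalogued, heterozygous | no match | removes it if the observed frequency falls inside | depends on depth |
| Missense SNV, uncatalogued, homozygous | no match | outside | kept |
| Indel, nonsense or captured splice variant, catalogued or not | does not apply | does not apply | kept |

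The last row needs no assumption about depth.

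**Step 2. Find which depths fit the calling rule.** More than 5 reads means at least 6. Six reads equal 2% at 6 / 0.02 = 300 reads. At lower depth the read count alone sets the floor (6 / 100 = 6%, 6 / 200 = 3%). The 2% limit therefore has an effect only from about 300 reads upward, and I take 300 to 1000 as the main range. Depth remains an assumption.

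**Step 3. Heterozygous uncatalogued missense SNVs.** Let X be the number of variant reads among n, X ~ Binomial(n, p). The share kept is P(X/n < 0.45 or X/n > 0.55). At n = 300 this is 1 - P(135 ≤ X ≤ 165).

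| Reads n | p = 0.50 | p = 0.48 (assumed mild reference bias) |
|---|---|---|
| 100 | 27.1% | 30.9% |
| 200 | 13.7% | 19.9% |
| 300 | 7.3% | 14.3% |
| 500 | 2.2% | 8.3% |
| 1000 | 0.1% | 2.7% |

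**Step 4. Homozygous uncatalogued missense SNVs.** With an assumed true frequency of 0.99, the chance of an observed value inside the window is about 8 × 10^-33 at 50 reads and smaller at higher depth. The window never removes them.

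**Step 5. Scale, for illustration only.** Section 7.1 plans 200 patients: (40 + 40 + 20) × 2 = 200. Assume each carries 0.1 to 1 uncatalogued heterozygous missense variant in the target genes. The number kept is 200 × variants per patient × leak:

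- 300 reads: 200 × 0.1 × 0.0733 = 1.5, up to 200 × 1 × 0.0733 = 14.7
- 500 reads: 0.45 to 4.5
- 1000 reads: 0.03 to 0.3

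The documents give no basis for a corresponding count of inherited indels or nonsense variants.

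**The case against.** **The protocol does not say outright that every surviving variant is called somatic.** It annotates the variants, discards an undefined ambiguous group, starts from named genes and refers to an in-house pipeline. Some inherited variants might be caught along the way. This stands as a limit on certainty: retention is inferred from the pipeline's stated purpose and from the Poisson test on non-silent mutations. But none of these steps is described as a germline test, and the rules that are so described are confined to missense SNVs.

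**The filter is more than a frequency window.** A reader might infer that all homozygous inherited variants, or most private missense variants, get through. The text does not support that. The database rule works at any allele frequency, so catalogued homozygous missense SNVs are removed. The heterozygous leak exceeds one quarter only at around 100 reads or fewer when reads are unbiased, where the 2% limit would have no effect.

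**Splice variants.** The kit is described as capturing coding exons, and coverage of intronic splice sites is not stated. Only those actually captured are at issue.

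**Importance.** The primary endpoint in section 5.1 is a count of laboratory tests, and neither section 5.1 nor section 5.2 contains a mutation measure. The Statistical analysis section describes the study as descriptive, and its paragraph on clinical outcomes names cytokines and microbiota, not mutations. The mutation correlation rests on section 2.2, which calls it preliminary. This stands, and it sets the weight of the point.

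**Omission or error?** It could be said that such detail belongs in a later analysis plan. That does not hold here, because the protocol itself fixes the variant class and the numerical limits.

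**Conclusion.** The point holds as a should-fix. Followed as written, the filter keeps inherited indels and nonsense variants, and any captured splice variants, as somatic at every depth, including those listed in a polymorphism database. This follows from the wording alone, provided that the undefined ambiguous discard and the annotation step do not happen to remove them.

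Uncatalogued missense SNVs are kept when homozygous. When heterozygous, about 7% are kept at 300 reads, 2% at 500 and 0.1% at 1000. These percentages assume binomial sampling, unbiased reads and an unstated depth; with mean frequency 0.48 they become 14.3%, 8.3% and 2.7%.

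The affected results are the per-gene Poisson test and the preliminary correlation in section 2.2. A reader might infer that the study's main result is compromised. It is not: neither the primary endpoint nor the sample size uses these calls. The number of patients who would be wrongly labelled cannot be estimated from the documents.

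**What to change.** Revise the filter rules in section 7.2, Molecular profiling analysis:

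1. Apply the database filter to all variant classes, using a prespecified population-frequency threshold and exempting known somatic hotspots.
2. For missense SNVs, replace the fixed window with a test of whether the read count, at its own depth, is compatible with 0.5. Add a rule for frequencies near 1.0. Keep the hotspot exemption.
3. Flag uncatalogued truncating variants and indels compatible with 0.5 or 1.0 as possibly germline. Report the Poisson test and the clinical correlations with and without them.

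This changes only analysis rules and needs no new samples or sequencing. The cost is that a few true somatic variants in dominant clones near 50% may be flagged or filtered. A depth-based test can also be wider than the present window at low depth. For example, a 99% interval around 0.5 at 100 reads is 0.5 ± 2.576 × √(0.25 / 100), or about 0.37 to 0.63. For that reason item 3 flags uncatalogued truncating variants and indels and does not remove them from the main set.
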